## Abstract

**Background:**

For complex diseases like cancer, pooled-analysis of individual data represents a powerful tool to investigate the joint contribution of genetic, phenotypic and environmental factors to the development of a disease. Pooled-analysis of epidemiological studies has many advantages over meta-analysis, and preliminary results may be obtained faster and with lower costs than with prospective consortia.

**Design and methods:**

Based on our experience with the study design of the Melanocortin-1 receptor (*MC1R*) gene, SKin cancer and Phenotypic characteristics (M-SKIP) project, we describe the most important steps in planning and conducting a pooled-analysis of genetic epidemiological studies. We then present the statistical analysis plan that we are going to apply, giving particular attention to methods of analysis recently proposed to account for between-study heterogeneity and to explore the joint contribution of genetic, phenotypic and environmental factors in the development of a disease. Within the M-SKIP project, data on 10,959 skin cancer cases and 14,785 controls from 31 international investigators were checked for quality and recoded for standardization. We first proposed to fit the aggregated data with random-effects logistic regression models. However, for the M-SKIP project, a two-stage analysis will be preferred to overcome the problem regarding the availability of different study covariates. The joint contribution of *MC1R* variants and phenotypic characteristics to skin cancer development will be studied via logic regression modeling.

**Discussion:**

Methodological guidelines to correctly design and conduct pooled-analyses are needed to facilitate application of such methods, thus providing a better summary of the actual findings on specific fields.

## Background

Since millions of Single Nucleotide Polymorphisms (SNPs) were identified by the SNP Consortium [1], a growing number of studies have reported the association of SNPs in candidate genes with several diseases. However individual studies of typical size usually have low statistical power to find true associations given the polygenic nature of most common diseases, leaving alone the various forms of potential interactions between genetic, phenotypic and environmental factors. The advent of genome-wide association studies allowed genotyping of hundreds of thousands of SNPs across the genome on a usually large number of subjects, but information on a wide spectrum of epidemiological and lifestyle factors were seldom collected, although the role of these factors in complex diseases is undoubtedly crucial.

Meta-analysis of genetic epidemiological studies has been adopted to increase the power of smaller candidate gene studies by summarizing results from multiple studies. However the lack of access to individual data precludes in-depth investigations, including analyses of gene-gene and gene-environment interaction, and appropriate stratified analyses. This may potentially lead to false-positive or false-negative results, or biased magnitudes of associations, as previously pointed out [2].

Pooled-analysis of the primary data has been shown to have critical methodological advantages over meta-analysis [3,4] and has been applied successfully in the genetic epidemiology field [4-11]. Pooled-analysis uses standardized definitions of cases, outcomes and covariates, as well as the same analytical methods, thus limiting potential sources of heterogeneity across different studies. It also allows investigators to better control for confounding factors, evaluate alternative genetic models and estimate the joint effect of multiple genes. Finally, population-specific effect and gene-gene and gene-environment interactions may be better assessed using pooled-analysis [12]. The pooling of data from observational studies has become more common recently, and different approaches of data analysis have been applied [13]. Methodological guidelines to correctly design and conduct pooled-analyses are needed to facilitate application of such methods, thus providing a better summary of the actual findings on specific fields. Moreover, the awareness of the potential problems connected with the establishment of international collaborations and data pooling might help investigators to avoid or overcome them.

We describe here our experience with the study design of an international pooled-analysis on Melanocortin-1 receptor gene, SKin cancer and Phenotypic characteristics (M-SKIP project). In the first part of the paper, we explain the procedures that were used to identify studies and to collect and standardize data. In the second part we describe the statistical analysis plan that we are going to apply, giving particular attention to methods of analysis recently proposed to account for between-study heterogeneity and to explore the joint contribution of genetic, phenotypic and environmental factors in the development of a disease.

## The M-SKIP project: rationale and aims

Melanocortin-1-receptor (*MC1R*, MIM#155555) is one of the major genes that determine skin pigmentation and it has been reported to be associated with risk of melanoma [14], possibly through the determination of the tanning response of skin to UV radiation [15-17]. However the relationship between some *MC1R* variants and melanoma also in darkly-pigmented European populations suggests that *MC1R* signaling may have an additional role in skin carcinogenesis beyond the UV-filtering differences between dark and fair skin [18]. In previous meta-analyses [14,19,20] authors found evidence of a significant association between melanoma, red hair and fair skin and the five *MC1R* variants R151C, R160W, D294H, D84E and R142H, and suggested a possible role in melanoma development, via non-pigmentary pathways, for I155T and R163Q variants. However, the specific contribution of each *MC1R* variant to melanoma development via pigmentary and non-pigmentary pathways could not be evaluated in meta-analyses due to the lack of individually joint information on *MC1R* variants and phenotypic characteristics.

The aim of the M-SKIP project is therefore to perform a pooled-analysis of individual data on sporadic skin cancer cases and controls with information on *MC1R* variants, in order to: 1) assess the association of *MC1R* variants with melanoma, basal cell carcinoma (BCC) and squamous cell carcinoma (SCC); 2) assess the association between *MC1R* variants and phenotypic characteristics, including hair and eye color, skin color, skin type, common and atypical nevi, freckles, and solar lentigines; and 3) perform stratified analyses on *MC1R* variants and skin cancer by phenotypic characteristics, and evaluate *MC1R*-phenotype interaction in skin cancer risk.

## Data collection and creation of the standardized dataset

### The identification of data sets and data collection

Published epidemiological studies on *MC1R* variants, melanoma, non-melanoma skin cancer (NMSC) and phenotypic characteristics associated with melanoma [21,22] were searched until April 2010 in the following databases: PubMed, ISI Web of Science (Science Citation Index Expanded) and Embase, using the keywords “MC1R” and “melanocortin 1 receptor” alone and in combination with the terms “melanoma”, “basalioma”, “basal cell carcinoma”, “squamous cell carcinoma”, “skin cancer”, “hair color”, “skin color”, “skin type”, “eye color”, “nevi”, “freckles”, and “solar lentigines”, with no search restriction. The computer search was supplemented by consulting the bibliographies of the articles and reviews. We also tried to identify unpublished datasets by personal communication with participant investigators, members of the Advisory Committee, and with attendees of scientific meetings. Unpublished datasets were evaluated by an internal peer-review process before inclusion.

We selected papers according to the following inclusion criteria: 1) observational studies on single-primary sporadic skin cancer cases with information on any *MC1R* variant or 2) control series with information on any *MC1R* variant and at least one phenotypic characteristic under study. Permanent exclusion criteria were: 1) populations selected for *MC1R* status or for other genetic factors, 2) studies including only familial and/or multiple-primary melanoma cases, because we wanted to study *MC1R*-melanoma association at a population level, therefore excluding cases for whom the role of genetics is probably stronger. In the first step of the project, we also excluded genome-wide association studies (GWAS), because their different study design and genotyping methodology would significantly increase the heterogeneity of our data; however GWAS with epidemiological data would be included in a next step of the project and their results would be compared with those of classical genetic epidemiological studies.

The original search provided 748 papers, among them 111 were considered potentially interesting and full-text articles were retrieved and evaluated. We excluded 49 articles for the following reasons: duplicate populations (N = 20), no data on outcome (case/control status or any of the studied phenotypic characteristics) or on *MC1R* variants (N = 12), case reports, commentaries or reviews (N = 6), GWAS (N = 6), populations selected for genetic factors (N = 4) and multiple primary melanoma cases only (N = 1). The remaining 62 independent studies were considered eligible for inclusion in the pooled-analysis.

For each independent study, we identified the corresponding investigator and retrieved his/her contact information. Each investigator was invited to join the M-SKIP project: this required them to sign a participation form and a document attesting to approval of the study guidelines, and then to provide their data in electronic form without restrictions on format. A detailed list of variables relevant for skin cancer was provided and, for each available variable in the list, the authors were required to compile a form with a clear and complete description on how it was collected and coded. Investigators did not send any personal identifier with data, but only identification codes. Finally, investigators were asked to send a signed statement declaring that the original study was approved by an Ethic Committee and/or that study subjects provided a written consent to participate in the original study.

Data collection started in May 2009 and was closed in December 2010. During this period, 43 investigators were contacted and invited to share data. Thirty-one (72%) agreed to participate and provided data on 28,998 subjects, including 13,511 skin cancer cases (10,182 melanomas) and 15,477 controls from 37 independent published [19,23-62] and 2 unpublished studies. Both the unpublished datasets came from investigators who were originally contacted for their published data and who had further data of (still) unpublished studies. Among the 12 non-participant investigators, seven did not reply to our invitation letter, three were not able to retrieve the original dataset and two were not interested in the project. The total number of skin cancer cases and controls from the 25 independent studies [63-95] of non-participant investigators was 5,135 and 8,262, respectively. The study design was case–control for 13 studies, control-only for 11 studies, and case-only for one study.

### Quality control, data coding and creation of the standardized dataset

We inspected the data for completeness and resolved inconsistencies with the investigator of each study. A number of subjects were excluded due to the following reasons: multiple-primary melanoma cases (N = 1596), missing data on *MC1R* variants (N = 1081), non-skin melanoma cases (N = 150), subjects with atypical mole syndrome and no skin cancer (N = 58), non first-primary melanoma cases (N = 24), familial melanoma cases, defined as subjects with two first-degree relatives or three or more any-degree relatives with melanoma (N = 25), other reasons including: unknown case/control status, duplicate subjects, or inappropriate controls (N = 232).

The following study-related variables were recoded uniformly: study country, study design, source of controls, application of case–control matching, methods to define phenotypic characteristics, genotyping methodology, whether genotyping was done in the same center for cases and controls and was blinded for case/control status, and DNA source. These variables were not used to assign a quality score to each study, but will be taken into account in meta-regression and sensitivity analyses. In addition, the variables listed in Table 1 were retrieved from each study if available, checked for quality, recoded in a standardized manner and entered in the main database. Finally, data on *MC1R* variants were entered for each subject. Quality controls and data coding were performed independently by two investigators, and inconsistencies were solved via consensus.

**Table 1 T1:** List of the main variables, number of original studies and related subjects per variable

**Variable**	**Studies (%) N = 39**	**Melanoma cases (%) n = 7806**	**NMSC cases (%) n = 3151**	**Controls (%) n = 14875**
Age	37 (95%)	7761 (99%)	3150 (100%)	14550 (98%)
Gender	39 (100%)	7801 (100%)	3151 (100%)	14853 (100%)
Ethnicity	38 (97%)	6770 (87%)	3142 (100%)	13833 (93%)
Body mass index	8 (21%)	557 (7%)	1380 (44%)	2226 (15%)
Smoking status	6 (15%)	2266 (29%)	419 (13%)	2286 (15%)
Intermittent sun exposure	21 (54%)	4493 (58%)	1266 (40%)	2286 (15%)
Continuous sun exposure	21 (54%)	4909 (62%)	741 (24%)	1938 (13%)
Sunburns	25 (64%)	4210 (54%)	1288 (41%)	2968 (20%)
Artificial UV exposure	16 (41%)	3842 (49%)	298 (9%)	1058 (7%)
Family history of skin cancer	27 (69%)	6660 (85%)	1289 (41%)	3318 (22%)
Family history of cancer other than skin	19 (49%)	4445 (57%)	371 (12%)	1630 (11%)
Melanoma body site	24 (62%)	6271 (80%)	NA	NA
Melanoma histology	19 (49%)	4868 (62%)	NA	NA
Breslow thickness	24 (62%)	5907 (76%)	NA	NA
Hair color	34 (87%)	6841 (88%)	2590 (82%)	11889 (80%)
Eye color	31 (79%)	5990 (77%)	2456 (78%)	10720 (72%)
Skin color	23 (59%)	3517 (45%)	826 (26%)	2963 (20%)
Skin type	31 (79%)	6590 (84%)	1992 (63%)	4540 (31%)
Common nevi	19 (49%)	3817 (49%)	442 (14%)	1181 (8%)
Atypical nevi	11 (28%)	2681 (34%)	642 (20%)	1447 (10%)
Freckles	21 (54%)	4028 (52%)	737 (23%)	2333 (16%)
Solar lentigines	6 (15%)	1419 (18%)	442 (14%)	1088 (7%)

*NA* = not applicable; *NMSC* = non melanoma skin cancer.

Some variables were collected in different ways in different studies. We report here as an example the rules we used to standardize sun exposure variables, in order to provide suggestions on how to recode variables with highly heterogeneous assessment among studies.

Intermittent and continuous sun exposure was coded as hours of exposure per day if the information was structured in this way. If not, we converted it to hours/day on a scale of 0 as no exposure and 6 as the maximum hours of exposure per day. For example, for datasets with four classes of exposure (never, seldom, often, always), we recoded the classes as 0, 2, 4, 6 hours/day. If individual sun exposure was collected over different time periods, we calculated the average exposure weighting for years of exposure in each time period. Other continuous variables (i.e. days of exposure per year, average hours of exposure per year) were converted to hours/day using the following algorithm:

1) calculate the variable mean on all the study subjects as:

(1)$$\mu =\sum_{i=1}^{n}x_{i}/n$$

where *x*_*i*_ is the measure of the continuous variable on subject *i*, and *n* is the study sample size;

2) calculate the average hours of exposure/day (*ν*) over all the datasets with the variable coded (or recoded) in this way as in 1);

3) recode each observation basing on the proportion $x_{i}:\mu ={\hat{x}}_{i}:\nu$ as:

(2)$${\hat{x}}_{i}=\nu x_{i}/\mu$$

4) set as 6 (maximum hours of exposure per day) the value of all calculated values greater than 6.

The assumption underlying this coding was that the average sun exposure pattern for study subjects was similar for different studies (and countries). Since we will use this variable only for confounding adjustment and/or effect modifier analyses, the purpose was to regroup subjects with a similar pattern of sun exposure, although the precise individual amount of sun exposure could not be estimated.

As a general rule, when a variable (i.e. common nevi count) was collected into classes, we recoded each class by using its median. The maximum numbers for open categories were chosen according to the available M-SKIP data.

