### Joint association of MC1R and phenotypic characteristics with skin cancer risk

Stratified analysis for the association of *MC1R* variants with each skin cancer type will be performed for different phenotypic characteristics. The hypothesis of homogeneity of ORs among strata will be verified using the Breslow-Day test [102].

In order to identify combinations of *MC1R* variants and phenotypic characteristics associated with each skin cancer type, we will perform logic regression, a recently proposed tree-based statistical method intended for binary predictors [103]. This approach is particularly useful for detecting subpopulations at high or low risk of disease, characterized by high-order interactions among covariates, and thus the methodology could be well applied to the study of complex diseases like cancer. First, we will dichotomize continuous and categorical variables by choosing appropriate thresholds and by creation of dummy variables. For phenotypic characteristics we will define dummy variables in order to 1) have as much differentiation as possible in hair and eye color, and 2) separate the extreme classes of skin type and common nevi count from intermediate classes, because it has been suggested [21] that in the meta- and pooled-analysis setting misclassification affects the intermediate classes of exposure more than the extreme ones. Let *X*_*1*_*, X*_*2*_*,…, X*_*p*_ be the binary predictors obtained by dichotomization, and let *Y* be the binary response variable (case/control status). The appropriate logic regression model can be written as:

(8)$$\text{logit}(Y=1|X_{1},X_{2},\ldots ,X_{n})=\alpha +\sum_{j=1}^{k}\beta_{j}L_{j}$$

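### The atypical mole syndrome exclusion applies only to people without skin cancer, so nevus main effects may be biased upward

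*Protocol article*

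**What the plan says.** The section on quality control, data coding and creation of the standardized dataset lists the subjects removed after receipt. One group is "subjects with atypical mole syndrome and no skin cancer (N = 58". The others are "multiple-primary melanoma cases (N = 1596), missing data on *MC1R* variants (N = 1081), non-skin melanoma cases (N = 150", then "non first-primary melanoma cases (N = 24", familial cases defined as "subjects with two first-degree relatives or three or more any-degree relatives with melanoma (N = 25", and a residual group covering "unknown case/control status, duplicate subjects, or inappropriate controls (N = 232". No entry names skin cancer cases with the syndrome, and no reason is given for the syndrome rule.

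The rationale and aims section counts "common and atypical nevi, freckles, and solar lentigines" among the phenotypes. The section on joint association plans analyses stratified by phenotype and logic regression. It keeps the extreme classes of common nevus count apart from the middle ones as binary predictors, and says of the method: "This approach is particularly useful for detecting subpopulations at high or low risk of disease". The example tree in Figure 1 has more than 50 common naevi as one of its terms. The risk of the subpopulations found is then to be estimated by the two-stage method, and structural equation models are also planned.

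On intake, the data collection section reports 28,998 subjects, "including 13,511 skin cancer cases (10,182 melanomas) and 15,477 controls".

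**The concern.** Whether a person with the syndrome stays in the dataset depends, as written, on whether that person has skin cancer. The syndrome marks the upper end of a variable that later serves as a predictor. If such people are trimmed from ordinary controls and kept among cases, the control odds of a high nevus class fall and the nevus-cancer odds ratio rises, with no biological cause.

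The results at stake are those in which nevi act as a risk factor in their own right: which nevus terms logic regression selects and their coefficients, the risk reported for a nevus-defined subgroup, and the nevus-to-cancer path in the structural equation models. Few controls have nevus data, so a small number of removals could matter there.

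**Working it through.** **Subject flow.** The exclusions sum to 1,596 + 1,081 + 150 + 58 + 24 + 25 + 232 = 3,166. Then 28,998 − 3,166 = 25,832, which equals the final dataset: 7,806 melanoma + 3,151 NMSC + 14,875 controls = 25,832. The list closes exactly, so any syndrome exclusion of cases could sit only inside the 232 residual removals, whose named reasons do not include it.

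**How the 58 were tallied at intake.** 13,511 + 15,477 = 28,988, which is 10 short of 28,998. The 58 have no skin cancer. If none was tallied as a case, at most 10 lay outside both groups and at least 58 − 10 = 48 were counted as controls.

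**Share of controls.** 58/14,875 = 0.4% of all controls. Table 1 gives 1,181 controls with common-nevi data and 1,447 with atypical-nevi data; 58/1,181 = 4.9% and 58/1,447 = 4.0%.

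**Effect on the nevus odds ratio.** Let n be the controls with nevus data after exclusion, p the share of them in the high-nevus class (not given in the article, so assumed), and m the number of removed subjects who were ordinary controls with nevus data in that class. Put a = np and b = n − a. The control odds are a/b as planned and (a + m)/b with the m restored. Cases do not change, so exclusion multiplies the crude nevus odds ratio by (a + m)/a.

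| Variable (n) | m | p = 5% | p = 10% | p = 20% | p = 30% |
|---|---|---|---|---|---|
| Atypical nevi (1,447) | 58 | 1.80 | 1.40 | 1.20 | 1.13 |
| Atypical nevi (1,447) | 48 | 1.66 | 1.33 | 1.17 | 1.11 |
| Atypical nevi (1,447) | 10 | 1.14 | 1.07 | 1.03 | 1.02 |
| Common nevi (1,181) | 58 | 1.98 | 1.49 | 1.25 | 1.16 |
| Common nevi (1,181) | 10 | 1.17 | 1.08 | 1.04 | 1.03 |

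Example: for atypical nevi at p = 5%, a = 72.35, and (72.35 + 58)/72.35 = 1.80. With m = 0 the factor is 1.

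**Effect on the MC1R odds ratios.** Suppose that in nevus class j a fraction s(j) of non-cases is kept, whatever their MC1R genotype. Carriers and non-carriers among the controls of that class shrink by the same s(j), so the carrier odds, and with them the MC1R odds ratio in that class, do not change. The ratio of these odds ratios between classes, which is the multiplicative interaction, does not change either. Only the nevus odds ratio moves.

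**The case against.** A reader might infer that nevus-defined risks are inflated. The documents do not show that. The article calls the 58 subjects, not controls, and lists inappropriate controls separately; this fits a distinct series of syndrome patients as well as it fits ordinary controls. If they were enrolled because of the syndrome, keeping them would over-represent nevi among non-cases, and removing them is right. That objection stands. So does the point that a condensed article may leave recruitment detail to the full protocol, so its absence is no fault in itself.

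The count of at least 48 helps only so far. It uses labels as received, in an article whose totals differ slightly elsewhere: the abstract has 14,785 controls against 14,875 in the data description, and Table 2 totals 7,808 melanomas against 7,806. Being tallied as a control shows that a person was a non-case, not that the person was sampled from the controls' source population.

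Retention of syndrome cases is inferred from the list's silence, and their number is unknown. Removing 1,596 multiple-primary and 25 familial cases may have taken some of them out.

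A reader might also infer that the stratified and interaction analyses of aim 3 are biased. The algebra above says they are largely protected, provided removal is independent of MC1R within nevus class.

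Finally, the factors come from one crude pooled table. In the two-stage method only the estimates from studies that supplied some of the 58 would move. If those were among the 6 control-only studies, no study-specific cancer odds ratio moves at all.

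What the objection does not remove is the rule itself: it is conditional on outcome, it has no counterpart for cases, and it acts on a studied variable. Even the benign reading needs cases to have been recruited independently of the syndrome. Where a study recruited both groups through it, dropping only the non-cases still pushes the nevus odds ratio up.

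**Conclusion.** The point holds as a possible upward bias in nevus main effects, not as a demonstrated one. It concerns the nevus terms in logic regression, the risks of nevus-defined subpopulations, and the nevus-to-cancer path in the structural equation models. The MC1R main effects are hardly touched, since the 58 are 0.4% of controls. The MC1R odds ratios within nevus strata and the MC1R-by-nevus interaction are largely safe under the independence condition stated.

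The size depends on facts the article does not give: how the 58 were recruited, how many had nevus data, and how common the high-nevus class is among controls. The upper range of about 1.2 to 1.8 for atypical nevi, reaching 1.98 for common nevi at 5% prevalence with all 58 counted, is a crude worst case. With 10 qualifying subjects the effect is small, and under the separate-series reading with independently recruited cases it is nil. The matter is worth correcting before the nevus-related analyses are run, because the remedy is cheap.

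**What to change.** Make the syndrome rule independent of case status within each contributing study, and state the reason for it.

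- Keep those of the 58 who were sampled by their study's ordinary control procedure.
- Where subjects were recruited because of the syndrome, leave out both the cases and the non-cases recruited that way.
- Where recruitment cannot be established, report the nevus-related logic-regression, subpopulation-risk and structural-equation results as sensitivity analyses: once with the 58 restored, and once with identifiable syndrome cases also removed.

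The cost is one query to the contributing investigators and a rerun of those analyses. The 58 records are already held, so no new data collection is needed.

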**Figure 1 F1:**
[figure not shown]
**Example of a logic tree representing the Boolean expression “*****more than 50 common naevi*****V [*****skin type IV*****Λ (*****MC1R R151C*****V*****brown hair*****)]”.**

The searching for the optimum combinations of *MC1R* variants and phenotypic characteristics mostly associated with skin cancer will be undertaken by a (stochastic) simulated annealing algorithm [104-106]. This algorithm has a good chance to find a model that has the best or close to best possible score but, in the presence of noise in the data, typically overfits data. In order to select the best model, application of a combination of cross-validation and randomization tests has been suggested [104,105].

In an explanatory setting, at risk gene-phenotype combinations will be identified among a very large number of possible combinations by logic regression-based methods recently proposed [106,107]. The skin cancer risk of the identified subpopulations will be estimated within the pooled-analysis context using the two-stage analysis previously described.

Structural equation models will be also applied to eventually clarify the independent and dependent role of *MC1R* variants on skin cancer by phenotypic characteristics.

Finally, the role of environmental exposure will be investigated by entering new covariates in the models, by subgroup analyses and by studying gene-environment and phenotype-environment interactions using traditional and new proposed methodologies [108].

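### The sun-exposure recode gives every rescaled study the same mean, over cases and controls together, so planned effect-modifier analyses that compare or pool recoded hours across studies rest on an untested assumption

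*Protocol article*

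**What the plan says.** The rule is in the Protocol article, section on quality control, data coding and creation of the standardized dataset. Exposure already in hours/day is kept, and classed exposure is mapped onto a 0 to 6 scale. For the rest: "Other continuous variables (i.e. days of exposure per year, average hours of exposure per year) were converted to hours/day using the following algorithm".

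The steps are:

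- mu, equation 1: "calculate the variable mean on all the study subjects as" the sum of the values divided by the study's sample size. Cases and controls are not separated.
- nu: "calculate the average hours of exposure/day" over all datasets coded, or already recoded, in hours/day.
- Equation 2: "recode each observation basing on the proportion", that is, recoded value = nu × x / mu.
- Cap: "set as 6 (maximum hours of exposure per day) the value of all calculated values greater than 6".

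The text then states the premise ("The assumption underlying this coding was that the average sun exposure pattern for study subjects was similar for different studies (and countries"), limits the variable to confounder adjustment and effect-modifier analyses, and says that "the purpose was to regroup subjects with a similar pattern of sun exposure". It concedes that individual amounts cannot be recovered.

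The section on the joint association of MC1R and phenotypic characteristics later says that "the role of environmental exposure will be investigated by entering new covariates in the models, by subgroup analyses", and adds gene-environment and phenotype-environment interactions. The two-stage section plans to compare analyses using original covariates with analyses using recoded ones.

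**The concern.** The recode is meant to place subjects with similar exposure together. Between two rescaled studies it does so only if the studies truly have the same mean exposure. If they do not, a subject at the average of a low-sun study and one at the average of a high-sun study receive the same hours/day. Table 2 spans Northern Europe, Southern Europe, North America and Australia, and the article offers no evidence that the means are equal.

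Taking mu over cases and controls together adds a second dependence. If cases and controls differ in exposure, mu moves with the proportion of cases sampled, so the same control gets a different recoded value in studies with different case fractions. Table 3 lists 21 case-control, 11 case-only, 6 control-only studies and 1 cohort. A rescaled case-only study and a rescaled control-only study would both be set to nu.

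At stake are results that treat recoded hours as a common unit: strata cut at one hours/day threshold, interaction coefficients per hour averaged over studies, and combined-dataset models. Equation 3 has a single intercept for all studies, so between-study differences in the recoded variable would enter such a model directly.

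**Working it through.** **What follows from the equations alone.** The mean of the recoded values in a study is nu × mean(x) / mu = nu × mu / mu = nu. This is exact before the cap, whatever the true mean. The article reports neither nu nor any study mean, so it has no figure of its own to reproduce.

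**What is not affected.** Within a study nu/mu is one constant. An interaction coefficient and its standard error are both multiplied by mu/nu, so their ratio z does not change, nor does the exposure-adjusted gene effect. A simulation of three studies confirms this. Assumptions: 60,000 subjects each; gamma exposure with shape 2 and means 1, 2.5 and 4 h/day; 20% carriers; true interaction 0.15 per hour; nu = 2.5.

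| True mean | Interaction z: original | rescaled | rescaled and capped | Adjusted gene log OR: original | rescaled | capped |
|---|---|---|---|---|---|---|
| 1 | 3.03 | 3.03 | 2.66 | 0.525 | 0.525 | 0.525 |
| 2.5 | 11.66 | 11.66 | 11.71 | 0.803 | 0.803 | 0.803 |
| 4 | 19.53 | 19.53 | 19.52 | 1.067 | 1.067 | 1.066 |

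**What is affected: the pooled per-hour interaction.** In expectation each study's coefficient becomes true value × mu/nu. With a common true value of 0.15 and nu = 2.5:

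| Assumed true means (h/day) | Recoded coefficients |
|---|---|
| 2.5, 2.5, 2.5 | 0.15, 0.15, 0.15 |
| 2, 2.5, 3 | 0.12, 0.15, 0.18 |
| 1, 2.5, 4 | 0.06, 0.15, 0.24 |

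For the last row the arithmetic is 0.15 × 1/2.5 = 0.06 and 0.15 × 4/2.5 = 0.24. The recode itself creates the four-fold spread. The simulated estimates, with sampling error, were 0.112, 0.158 and 0.174 on the true scale and 0.045, 0.158 and 0.276 after rescaling.

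**What is affected: a common cut-point.** A true 2 h/day is recoded as 2.5 × 2/mu. That is 5.0, 2.0 and 1.25 for means 1, 2.5 and 4. For a gamma with shape 2 and mean m, the share above 3 is exp(−6/m) × (1 + 6/m).

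- Means 1, 2.5, 4: truly 1.7%, 30.8% and 55.8% above 3 h/day.
- Means 2, 2.5, 3: truly 19.9%, 30.8% and 40.6%.
- After recoding: 30.8% in every study, in both sets.

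The cap truncates about 5% of subjects in each of these studies and lowers each mean from 2.50 to 2.43.

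**What is affected: the case fraction.** Assume true means of 3 h/day in cases and 2 in controls, the same in every study. With case fraction f, mu = 3f + 2(1 − f), and with nu = 2.5:

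| Study | mu | Recoded control mean | Recoded case mean |
|---|---|---|---|
| Control-only | 2.0 | 2.50 | none |
| 20% cases | 2.2 | 2.27 | 3.41 |
| 50% cases | 2.5 | 2.00 | 3.00 |
| Case-only | 3.0 | none | 2.50 |

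Within each mixed study the case-to-control ratio stays 1.5. Across studies the contrast is lost: cases in the case-only study and controls in the control-only study both average 2.50. Table 1 shows that subjects with sun data are mostly cases: for intermittent exposure (4,493 + 1,266) / (4,493 + 1,266 + 2,286) = 72%, and for continuous exposure (4,909 + 741) / (4,909 + 741 + 1,938) = 74%.

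**The case against.** The strongest reply is that the preferred analysis is the two-stage one, in which odds ratios are estimated inside each study. There the scale factor is harmless, case-only and control-only studies supply no skin-cancer odds ratio, and the case fraction drops out. This stands, and it removes confounder adjustment and within-study interaction tests from the concern.

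Second, the article does not commit to a common cut-point or a pooled per-hour coefficient for sun exposure; a fuller plan might avoid both. This also stands, and makes the harm conditional. But the recode exists to supply a common hours/day scale, and the article names effect-modifier and subgroup uses without limiting them to within-study contrasts.

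Third, the assumption is disclosed and original and recoded covariates will be compared. Disclosure is to the article's credit but is not a test. The planned comparison is described for the first-stage confounders and is not tied to the gene-environment analyses; days/year and hours/year cannot be pooled per unit in original form.

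Fourth, within-study categories also code alike two subjects of equal rank in a low-sun and a high-sun study. True: they do not recover absolute exposure. They remove the appearance of a common unit and, if cut in controls, the dependence on case fraction.

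A reader might go further and apply Table 3's counts by study design to estimate how far the overall case-control difference in sun exposure is diluted. The documents do not support that. Table 1 shows exposure data for only 2,286 (intermittent) or 1,938 (continuous) controls out of 14,875, only part of these would be rescaled, and the combined-data contrast is not the preferred analysis.

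**Conclusion.** The point holds in a limited form. It is certain that each rescaled study is given mean nu before the cap, and that mu mixes cases and controls. It is conditional that this distorts results: mean exposure or case fraction must differ between rescaled studies, and the analysis must use a common hours/day cut-point, a pooled per-hour interaction or a combined dataset. If true means are equal and the case mix is the same, nothing is lost. With means of 2 to 3 h/day a common 0.15 per hour spreads to 0.12 to 0.18; with means of 1 to 4, to 0.06 to 0.24. All these exposure means, the gamma shape and nu are assumptions.

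Two stronger readings should be avoided. A reader might infer that all sun-exposure data are forced to one mean; studies in hours/day or in classes are not, and the article does not say how many are rescaled. A reader might also infer that a stated objective fails; the three numbered aims concern MC1R with skin cancer, with phenotype, and their interaction. Gene-environment work is a planned additional analysis. The change is worth making because those analyses are announced and the article offers this recode as a suggestion for handling heterogeneous variables.

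**What to change.** - Compute mu in controls for every study that has controls, and take nu on the same basis. In the example above, controls then recode to 2.5 × 2/2 = 2.50 and cases to 2.5 × 3/2 = 3.75 before the cap, whatever the case fraction.
- Do not use rescaled values from case-only studies in exposure contrasts across studies.
- For effect-modifier, subgroup, gene-environment and phenotype-environment analyses, replace recoded hours by within-study categories, for example tertiles cut in that study's controls. Pool only within-study interaction estimates.
- Describe these results as relative to the study's own exposure level, not as hours/day.
- Repeat them with the present recode as a sensitivity analysis, and report which studies were rescaled and their case fractions.

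The cost is a recode of data already in hand. Results will be in relative categories, absolute differences between countries will still not be recovered, and case-only studies leave these analyses. Two-stage confounder adjustment can stay as planned.
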